### MRI

All participants will undergo a series of MRI sessions before, and 1-month and 6-months after CWMT. All structural and fMRI studies will be performed on a research-dedicated 3 Tesla Siemens TIM Trio scanner (VB17), using a 12-channel phase-array head coil.

#### Structural MRI

A 3D magnetization-prepared rapid gradient-echo scan will be performed (sagittal, TE/TR/TI = 4.9 ms/2.2 s/1 s, 7° flip angle, 1 mm resolution covering the whole-brain). Next, a 3D-T2-weighted sequence (SPACE) will be acquired (sagittal, TR/TE = 3200/447 ms, field of view = 320 mm, 1.0 × 1.0 × 1.0 mm resolution, 192 slices, generalized autocalibrating partially parallel acquisitions (GRAPPA) = 2, 3:52 min). Both scans will be reviewed to screen for possible brain lesions or structural abnormalities.

#### BOLD-fMRI

The entire brain is scanned continuously with an axial single-shot gradient-echo echo planar imaging sequence (TE/TR30/2500 ms, 20 cm field of view, 64 × 64 resolution, ≈35 × 3 mm slices, no gap) with motion correction. An electronic pulse from the scanner synchronizes the fMRI scan and stimulus presentation. Scans with excess motion (more than ±1 mm translations or ±1° rotations) are repeated immediately*.*

#### fMRI paradigms

Each subject will perform six different tasks during the fMRI scans. Tasks will be displayed using a binocular video display (Nordic Neurolab Inc.™). Subjects will be trained first outside the scanner to ensure that they will be able to perform the tasks well during the scans (>80 % accuracy, monitored during the scan). Scans with unacceptable response accuracy will be repeated immediately.

#### Working memory (n-back)

This task uses a block design (30 s of alternating control and activation periods, including 3 s of instruction). During activation periods, a random sequence of single letters is presented (1 letter per second for 500 ms). Subjects are trained to press a button whenever the current letter is identical to the letter 1 or 2 events back, or for any number (0-back). The targets (i.e., 0-, 1-, or 2-back events) are random events (5/30 s block). Button events are used to determine accuracy and reaction times. During control periods, subjects passively view a random sequence of symbols (non-letters), with matching font size, brightness, and timing.

#### Visual attention (ball tracking)

These tasks evaluate non-verbal visual attention [66, 67], which we also expect to improve after working memory training. Subjects mentally track two, three, or four target balls that are highlighted briefly among 10 randomly moving, colliding balls. Every 12.5 s, another set of balls is highlighted for 1 s and the subjects push a button if subjects agreed that the balls were the original targets (performance monitoring). Periods of tracking (1 min) alternate with passive viewing (1 min) of balls that move in the same random motion without highlighting (block design: 1 min/period × 2 periods × 3 blocks).

### Genotyping

Samples of DNA will be extracted from whole blood or saliva collected in EDTA-tubes using DNeasy Blood & Tissue Kit (catalog number 69506, Qiagen Inc., Valencia, CA, USA). Genomic DNA will be subjected to restriction fragment length polymorphism PCR to genotype each participant for *LMX1A* at rs4657412 as described previously [68]. Specifically, approximately 3ng of genomic DNA will be amplified for LMX1A using the primer LMX-5': 5'-CTCGCCTCCAGGAATGGGTGTTGTA-3' and LMX-3': 5'-GCCACGAGGAACTTGTGAGAGGGTT-3', and under the following conditions: denaturation at 94C for 5 min, followed by 30 cycles at 94 °C for 30 sec, annealing at 64 °C for 30 sec, and extending at 72 °C for 30 sec. 15 ul of the amplification products will be digested by 2.5U of MslI (R0571s, New England Biolabs, Beverly, MA) for 2 h at 37°C. The digested  PCR products will be then analyzed on a 4 % agarose gel and visualized using GelGreen® Nucleic Acid Gel Stain (89139-144, Biotium, Hayward, CA).

### Cerebrospinal fluid cytokines/chemokines and dopamine/dopamine-related metabolite measurements

Lumbar punctures will be performed at baseline and 1 month after CWMT in participants who have agreed to spinal taps. The cerebrospinal fluid will be collected, aliquoted into 0.5 ml portions, and swiftly frozen at −80 °C. Measurements for both ELISAs and monoamines will be run in batches.

#### ELISA

We will quantify fractalkine, IL-1α, MCP-1, IP-10, IL-8, and IL-4 using the RayBio ELISA kits (RayBiotech, Inc., Norcross, GA, USA). Since fractalkine concentration is relatively low even in normal serum and plasma, and may not be detected in the RayBio assay, we plan to use the Human Fractalkine ELISA kit (ADIPO Bioscience, Inc., Santa Clara, CA, USA), which is reportedly more sensitive [69].

#### Cerebrospinal fluid dopamine and dopamine metabolite levels

These will be measured using HPLC assays [70] with electrochemical detectors and using principal component analysis precipitation to remove proteins and stabilize small molecule analytes. Internal standards will be used to measure monoamines and their metabolites, including norepinephrine, dopamine and its metabolites, 3,4-dihydroxyphenylacetic acid and homovanillic acid, as well as serotonin (5-hydroxytryptamine) and its metabolite, 5-hydroxyindole-3-acetic acid.

### Statistical analysis

All analyses will be performed using SAS, using repeated-measures analysis of variance (ANOVA) as the primary model (co-varied for age and sex). The baseline (initial) values of all key variables will be tested for normality prior to analysis. Appropriate transformations (or non-parametric tests) will be used as necessary. The statistical significance will be determined using a modified Bonferroni procedure for multiple tests [71]. The procedure will have a type I error probability equal to 0.05 for independent tests.

Neurocognitive assessments will be tested using appropriately constructed contrasts within a 2 × 2 repeated-measures ANOVA model. HIV status (and HAND status for subgroup analyses) and training condition (adaptive versus fixed) will be across-subjects variables, and time (baseline, 1-month, 6-months) will be within-subject variables. Analyses will be co-varied for subject age, sex, and other co-variates as needed (e.g., depression scores). Subjects trained in both the adaptive and fixed training will have the training condition as a within-subject variable.

The fMRI time series will be analyzed using Statistical Parametric Mapping software (SPM8, Welcome Department of Cognitive Neurology, UK). After spatial normalization and smoothing, maps of brain activation and differential changes in activation (repeat − baseline) will be calculated for each subject and task, using a fixed-effects model with a block design. In a subsequent random-effects analysis, differences between groups on BOLD signal changes will be evaluated for each task (*t* tests or ANOVA). Statistical significance will be based on cluster-level significance at *P* < 0.05 corrected for multiple comparisons (voxel-level threshold *P* < 0.05, cluster size >100 voxels). Additionally, we will extract regional percentage BOLD-fMRI signals from cubic regions of interest (0.729 cm^3^) centered at cluster maxima, using a customized program written in Matlab. The extracted data will be imported into SAS, where a repeated-measures ANOVA model will be run to confirm and further evaluate the statistical parametric mapping findings.

For the genetic study, we will first determine the Hardy–Weinberg equilibrium for both allelic and genotype frequencies of the *LXM1A* gene in our cohort. To minimize the number of correlations, we will use repeated-measures ANOVA to select cognitive variables and extracted fMRI data that show changes from baseline to 6 months after CWMT (adaptive versus active control). We will assess the relationship of these variables with the *LMX1A* genotypes and with cerebrospinal fluid markers using ANCOVA. Repeated measure ANCOVAs and multivariate ANCOVAs will also be utilized.

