### Primary and secondary outcome measures

The main goal of this study is to examine the effectiveness of intensive adaptive working memory training for the treatment of HAND. The primary outcome measures will be the improvement index on CWMT, improvement on non-trained near-transfer working memory tasks, and changes on brain activation assessed with BOLD-fMRI during working memory and attention tasks. Secondary contrasts will evaluate genotype effects (*LMX1A*, TT(AA) versus TC(AG) or CC(GG)) on cognitive improvements and BOLD-fMRI. We will also assess CWMT-related improvements on self-reported depressive and various psychopathological symptoms, using the Center for Epidemiological Studies–Depression Scale Revised and Symptom Checklist–90 revised items, and on self-rated functionality, using the Independent Activity of Daily Living assessment and the Behavior Rating Inventory of Executive Function–Adult Version.

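### The fMRI cluster rule is called corrected at 5%, but voxel P<0.05 with a fixed extent above 100 voxels does not hold that rate

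*Protocol article*

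**What the plan says.** The Primary and secondary outcome measures section of the protocol article lists among the primary outcomes "changes on brain activation assessed with BOLD-fMRI during working memory and attention tasks". The Statistical analysis section sets the cluster-level significance of the maps at "0.05 corrected for multiple comparisons (voxel-level threshold *P* < 0.05, cluster size >100 voxels", with the voxel threshold and the extent in brackets. Group comparisons are described as follows: "differences between groups on BOLD signal changes will be evaluated for each task (*t* tests or ANOVA". The article does not say whether a t contrast is one- or two-sided. Maps are analysed "After spatial normalization and smoothing", with no kernel or resampled voxel size given. Signals are then extracted from "cubic regions of interest (0.729 cm^3^) centered at cluster maxima" and re-analysed by repeated-measures ANOVA in SAS to confirm the map findings. The fMRI paradigms section has six tasks per subject.

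**The concern.** The article fixes three things together: a voxel threshold, a cluster extent, and the error rate they are said to deliver. A voxel threshold of P<0.05 lets one voxel in twenty through under the null, and smoothing joins neighbouring survivors into clusters. How large such chance clusters grow depends on smoothness and voxel size, so one extent cannot give 5% in general. As a volume, 100 voxels is 100 × 27 mm³ = 2.7 cm³ at 3 mm but 100 × 8 mm³ = 0.8 cm³ at 2 mm.

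At stake is the type I error of a primary outcome. A false cluster could be reported as a gain in neural efficiency. The SAS step does not protect against this, because the regions are chosen from the same data that it then tests. Extracted fMRI values that pass a further ANOVA screen, again on the same subjects, go on to the genotype and cerebrospinal fluid analyses.

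**Working it through.** **Two readings.** (a) The bracket is itself the corrected rule. (b) The bracket gives the forming threshold and a minimum extent, and a corrected cluster-level P<0.05 is required as well.

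**Inputs from the article.** Claimed error 0.05; voxel P<0.05; more than 100 voxels. Acquisition is "20 cm field of view, 64 × 64 resolution, ≈35 × 3 mm slices, no gap", so the acquired voxel is 200/64 = 3.125 mm in plane by 3 mm. The extraction cube of 0.729 cm³ has a 9-mm side and equals 27 voxels of 3 mm (27 × 27 mm³ = 729 mm³), which fits 3-mm analysed voxels.

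**Assumptions, not in the article.** 3-mm voxels (also 2 mm and the acquired size); ellipsoidal search volume of 1,400 cm³ (also 1,200 and 1,800), which is 51,858 voxels; smoothness (FWHM) of 4-12 mm; stationary Gaussian noise; 18-neighbour connectivity. About 51,858 × 0.05 = 2,593 voxels pass by chance in a one-sided map.

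**Reading (a).** Share of null maps with at least one cluster above 100 voxels, 3-mm voxels, 1,400 cm³:

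| FWHM (mm) | One-sided P<0.05 | Two-sided or F map (0.025 per tail) |
|---|---|---|
| 4 | 0% | 0% |
| 5 | 12% | 0% |
| 6 | 58% | 1% |
| 7 | 92% | 22% |
| 8 | 99% | 59% |
| 10 | 99.5% | 98% |
| 12 | 100% | 100% |

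- Repeat runs with other random draws gave 51-66% at 6 mm and 9-13% at 5 mm (one-sided), and 1-2% at 6 mm (two-sided). Monte Carlo error with 200 maps is about 3-4 points mid-range.
- Acquired voxel size, one-sided: 48%, 97.5%, 100%, 100% at 6, 8, 10, 12 mm.
- 2-mm voxels: 100% at 6-12 mm, one- or two-sided.
- Volumes of 1,200 and 1,800 cm³ at 6 mm, one-sided: 53% and 74%.
- Both directions tested, each at one-sided 0.05: 86% at 6 mm, 100% from 8 mm.
- A simulated t map of 25 v 25 subjects: 65% at 6 mm, 100% at 8 mm (20 maps only).

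The claimed 5% is therefore not reproduced as a property of the rule. To hold 5% in a one-sided map at this threshold, the extent would have to be about 180-190, 360-400, 540-640 and 830-990 voxels at 6, 8, 10 and 12 mm.

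**Reading (b).** Random-field corrected P for a cluster of k voxels: P = 1 − exp(−E[m]·exp(−β·k^(2/3))), with β = (Γ(2.5)·R₃·ρ₃/E[N])^(2/3). Here E[m] is the expected number of clusters, E[N] the expected number of suprathreshold voxels, R₃ the volume in resels, and ρ₃ the three-dimensional Euler characteristic density at z = 1.645. Worked at 8 mm:

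- R₃ = 51,858 × 27/8³ = 2,734.7; ρ₃ = 0.0516; E[N] = 2,593
- E[m] = 1 × 0.05 + 34.7 × 0.0685 + 472.8 × 0.0749 + 2,734.7 × 0.0516 ≈ 178.8 (lower-dimensional resels from a sphere of equal volume, radius 69.4 mm)
- β = (1.329 × 2,734.7 × 0.0516/2,593)^(2/3) = 0.174
- k = 101: P = 1 − exp(−178.8 × exp(−0.174 × 21.7)) ≈ 0.98

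| FWHM (mm) | P of a 101-voxel cluster | Critical size | Simulated error of the random-field rule |
|---|---|---|---|
| 6 | 0.39 | 157 | 15% |
| 8 | 0.98 | 323 | 9.5% |
| 10 | >0.99 | 560 | 7.5% |
| 12 | >0.99 | 874 | 8.5% |

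Each error is from 200 one-sided maps. The standard error at 7.5% is √(0.075 × 0.925/200) = 1.9 points, so that value alone is not clearly above 5%. The average of the four, (15 + 9.5 + 7.5 + 8.5)/4 = 10.1% over 800 maps, is (standard error about 1.1 points). Every critical size exceeds 100, so over this range the extent filter never binds.

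**The case against.** The strongest defence is that the sentence names the corrected cluster-level P as the criterion and that the bracket only records software settings. That is a fair reading. Under it the excess error is moderate, about 7.5-15%, and an added minimum extent can only remove clusters. The defence does not restore 5%, though, and it leaves the 100 voxels with no part in the correction.

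The second defence is that kernel, voxel size and sidedness are details a condensed article may leave to the full plan. That stands, and their absence is not the fault. It also means no single error rate can be attributed to the protocol. A reader might infer that false clusters are almost guaranteed in every map, or that the error is 50-100% whatever the settings. The article does not support that. The 50-100% needs reading (a), a one-sided map and smoothness of 6 mm or more; near-certainty needs about 8 mm or more. The plan allows ANOVA, and an F map at 6 mm with 3-mm voxels gives only about 1-2%. On the other side, t tests are named first, the Aim 2 text predicts decreased activation, and F maps reach about 60% at 8 mm and 98% at 10 mm.

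Third, the genotype and cerebrospinal fluid analyses do not take clusters directly; an ANOVA on change from baseline selects the variables first. That is correct, but the screen uses the same data and is not an independent check.

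**Conclusion.** The concern holds in conditional form. Voxel P<0.05 with more than 100 voxels does not in itself give a corrected 5%, and the article says that it does, for a primary outcome. If the bracket is the whole rule, the error per null map is about 50-100% (one-sided, 6-12 mm), about 10% at 5 mm, and about 1-2%, 60% and 98% for two-sided or F maps at 6, 8 and 10 mm. If a random-field cluster P is also required, it is about 7.5-15%. These figures rest on 3-mm voxels, a 1.4-litre volume and stationary Gaussian noise. The two-sided figures cover a single contrast in both signs; F maps with more numerator degrees of freedom were not simulated. All rates are per map, and there are six tasks. The cognitive primary outcomes are unaffected.

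A reader might also infer that the pilot BOLD effect sizes behind the sample size came through this rule. The Participants section does not say how they were obtained, so nothing follows for them.

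**What to change.** Replace the bracketed rule with a cluster-forming threshold of P<0.001 and cluster-level family-wise P<0.05 over the whole brain. Use random-field theory, or permutation suited to each contrast: permuting training labels serves only adaptive versus control, and the HIV-status and pre-post contrasts need their own schemes. State the smoothing kernel, the analysed voxel size and the sidedness, and say that the corrected cluster P alone decides significance.

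Do not carry the 100-voxel extent over as the correction. With P<0.001 and 3-mm voxels it is stricter than needed: the simulated 5% extents are 11, 22 and 34 voxels at 6, 8 and 10 mm. With 2-mm voxels it can still be too lenient, with error of 2%, 8% and 17% at 8, 10 and 12 mm.

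Keeping P<0.05 with an extent simulated from the data's own smoothness would also hold 5%. The clusters required, about 180-990 voxels or 4.9-26.7 cm³ at 27 mm³ each, would then say little about location.

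The cost is a change of analysis settings, with no new data or visits. The loss is sensitivity to weak, diffuse change. Settle the rule before the interim fMRI results planned in the Dissemination plan are analysed.

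### The regional ANOVA meant to confirm the fMRI training effect is run at maxima chosen for showing that effect, so for that contrast it is circular and inflates the effect size.

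*Protocol article*

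**What the plan says.** The fMRI paragraph of the protocol article's Statistical analysis section sets out one sequence:

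1. For each person, "maps of brain activation and differential changes in activation (repeat − baseline) will be calculated for each subject and task".
2. In a random-effects step, "differences between groups on BOLD signal changes will be evaluated for each task".
3. Significance is judged at cluster level, P < 0.05 "corrected for multiple comparisons", with the rule given in brackets as "voxel-level threshold *P* < 0.05, cluster size >100 voxels".
4. Signal is then extracted from "cubic regions of interest (0.729 cm^3^) centered at cluster maxima".
5. The extracted values go into SAS, "where a repeated-measures ANOVA model will be run to confirm and further evaluate the statistical parametric mapping findings".

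The section on primary and secondary outcome measures lists change in BOLD activation among the primary outcomes. The genetic-study paragraph uses the extracted values again: it selects cognitive variables and "extracted fMRI data that show changes from baseline to 6 months after CWMT (adaptive versus active control"), then relates them to genotype and cerebrospinal fluid markers.

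The article describes no regions set in advance, independent localiser, split sample or restriction of the regional ANOVA to contrasts other than the selecting one.

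**The concern.** The cube is placed where the difference in change between groups is largest in these subjects, and the ANOVA then asks those same subjects whether the groups differ in change there. With two training arms and one change score, the group-by-time term of a repeated-measures ANOVA is the two-sample t test on the change score, apart from covariates. That is the contrast that chose the location, so a small P value is built in.

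Two things are at stake for Aim 2. A reader would take the regional result as a second, independent support for the whole-brain result, which it is not. The regional difference reported would also be biased away from zero, because each location was kept for being extreme. This is not a detail left to another document: the article states the region rule, the test and the purpose of the test.

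**Working it through.** **The plan's own figure.** The article states no error rate or effect size for the regional step, so there is nothing to reproduce.

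**Inputs from the article**
- Cube: 0.729 cm³ = 729 mm³; side = 729^(1/3) = 9 mm; 729/27 = 27 voxels of 3 mm.
- Acquired grid (BOLD-fMRI section): 200 mm/64 = 3.1 mm in plane, 3 mm slices.
- Expected at 1 month (Participants section): 50 HIV-positive and 52 seronegative. Within one serostatus group this is 50/2 = 25 or 52/2 = 26 per training arm; pooled over serostatus it is 102/2 = 51 per arm.
- Cluster rule: voxel P < 0.05 and more than 100 voxels.

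**Assumptions (not in the article)**
- Smoothing of 8 mm full width at half maximum, varied from 6 to 12 mm.
- Analysis voxels of 3 mm, and an ellipsoid brain of about 1,400 cm³.
- One-sided voxel threshold in each direction; no covariates.

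**Why the result is nearly forced.** With n per arm, the t statistic and the standardised difference d are linked by t = d / √(2/n).
- n = 25: √(2/25) = 0.283. The one-sided 5% point on 48 df is 1.677, so every voxel in a cluster already shows d of at least 1.677 × 0.283 = 0.47. The two-sided 5% regional test needs 2.011 × 0.283 = 0.57.
- n = 50: √(2/50) = 0.200. Every cluster voxel shows at least 1.661 × 0.200 = 0.33; the regional test needs 1.984 × 0.200 = 0.40.

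The cube sits on the peak of a cluster of more than 100 voxels, so clearing the slightly higher bar is close to automatic.

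**Null simulation.** Smooth Gaussian change maps with no true effect were generated for two arms. Clusters were found by the stated rule, a 9 mm cube was centred on each peak, and the cube mean was tested with a two-sided t test in the same subjects.

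| Per arm | Smoothing | Regions | P < 0.05 | P < 0.01 | Mean apparent d (true 0) |
|---|---|---|---|---|---|
| 25 | 6 mm | 46 | 100% | 87.0% | 0.96 |
| 25 | 8 mm | 310 | 100% | 92.6% | 0.99 |
| 25 | 12 mm | 431 | 100% | 86.5% | 0.93 |
| 50 | 8 mm | 150 | 99.3% | 92.0% | 0.68 |

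A separate repeat at 26 and 51 per arm gave 100% at P < 0.05, with apparent effects of about 0.96 and 0.67. The drop with sample size is as expected: 0.96 × √(25/50) = 0.68.

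**Comparators** (150 null maps, 8 mm, 25 per arm)
- Same subjects, selecting contrast: 1,119/1,121 = 99.8% significant.
- Same cubes, independent null subjects: 4.1%.
- Same cubes and subjects, a contrast orthogonal to the selecting one: 2.8%.
- Only the 8 of 150 maps whose largest cluster passed a true 5% family-wise size: 8 of 8 significant.

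The last line separates the two steps. A valid cluster correction limits how often a false cluster is declared, but it does not make the second test informative about the cluster.

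**The case against.** The strongest reply is that the regional ANOVA does not decide significance. The article bases that on corrected cluster-level inference and adds the extraction afterwards, so the regional step cannot turn a negative whole-brain result positive. That stands. A reader might infer that the plan yields a confirmed effect whenever nothing is there, but the near-certain confirmation is conditional on a cluster having been declared. How often that happens under the null depends on the cluster rule and the assumed smoothing, and is a separate matter.

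Secondly, the sentence has two purposes, and further evaluation can be legitimate. Direction, plots and contrasts orthogonal to the selecting one are not circular, as the 2.8% shows. This also stands, but the article does not separate these uses from confirmation. The six-month change is not fully orthogonal at a one-month maximum, because both changes share the baseline scan.

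Thirdly, a reader might infer that the genotype and cerebrospinal fluid analyses become false-positive. The genetic-study paragraph does carry selected, inflated change values forward, but genotype is a different factor from the one used for selection, and no inflated error rate has been shown for either analysis.

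Finally, a reader might infer that a later trial would be sized from these regional values. The Dissemination plan and Discussion say only that the findings may lead to a larger study.

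**Conclusion.** The point holds for the selecting contrast. Training by time, tested at the maxima of clusters chosen on training by time in the same subjects, is circular. Given a declared cluster, the regional test is significant in about 99 to 100% of cases under the null, against about 5% or less in independent subjects. The apparent effect is about 0.95 SD at about 25 per arm and about 0.67 SD at about 50 per arm when the true effect is 0.

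The significance rate barely moves over 6 to 12 mm of smoothing. The size of the inflation depends mainly on the number per arm, so the larger figure applies to a comparison within one serostatus group and the smaller to one pooled over serostatus. The figures rest on the assumed smoothing, voxel size and brain volume, and on a model without covariates. They also rest on reading the cluster maxima as those of the group comparison of change, which the order of the sentences and the stated aim of confirming those findings support.

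The harm is a second result that looks independent and is not, together with an inflated regional effect size for a primary outcome.

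**What to change.** 1. Keep inference on the training effect at the whole-brain level, with a cluster correction shown to hold its stated error rate.
2. Delete the claim that the regional ANOVA confirms the mapping result.
3. At training-effect maxima, report extracted values descriptively for the selecting contrast, with no P value and no effect-size claim. Contrasts orthogonal to the selection may still be tested there.
4. If a confirmatory regional test is wanted, run training by time in regions fixed independently of that contrast: coordinates listed before unblinding, or maxima of baseline task activation pooled over both arms. With baseline maxima, keep the claim to training by time, because a fall within one arm could be regression to the mean.
5. In the genetic-study paragraph, say that fMRI values chosen for showing training change are selected values and that their size is not an unbiased estimate.

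Items 1 to 3 and 5 are mainly changes to wording and reporting; checking the cluster correction uses existing data. Item 4 needs re-extraction from existing scans and no new data. Its downside is that effects outside the pre-set regions have no regional confirmation.
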